## Methods and analysis

3

### Preregistration and ethics

3.1

The present manuscript reports the clinical protocol phase of the preregistered NeuroPsychth program (OSF: 10.17605/OSF. IO/3RHK4); preregistered analyses and hypotheses are retained, with any phase-specific deviations transparently labeled. The study protocol was approved by the ethics committee of the University of Salzburg (reference number: GZ 41/2024 addendum). The study will be conducted in accordance with local legislation and institutional requirements. All participants will provide written informed consent prior to participation.

### Study design

3.2

This study uses a prospective, within-subject (repeated-measures) experimental design with block-randomized condition order. Each participant completes one laboratory session consisting of a brief regulatory challenge (stress induction), a resting-state baseline, and three auditory conditions presented in randomized order:

Mindfulness: body scanRelaxation: safe place guided imageryControl: podcast

All three conditions are approximately equal in duration (∼10 min each) and are delivered as spoken audio to ensure comparable sensory input across conditions. The full study procedure is illustrated in Figure 1.

**Figure 1 fig1:**
[figure not shown]
Full study procedure.

### Randomization and blinding

3.3

The three auditory conditions are presented in randomized, counterbalanced order using a predefined condition-order scheme implemented in the MATLAB experiment script. Separate condition-order matrices are generated before data collection for the ADHD and depression groups using a random number generator. In the script, each auditory condition is assigned a numerical code: body scan = 1, safe place imagery = 2, and podcast = 3. These numbers are condition codes, not order numbers. For example, [1 2 3] means body scan–safe place imagery–podcast, whereas [2 3 1] means safe place imagery–podcast–body scan. In the ADHD matrix, for example, participant 1 could receive [1 2 3], participant 2 [1 3 2], and participant 3 [2 1 3]. At the start of the experiment, the experimenter enters the participant’s diagnostic group and sequential within-group participant number. The MATLAB script then selects the corresponding row from the predefined matrix and presents the audio files in that order. This procedure supports a balanced distribution of condition orders as far as possible within each diagnostic group and ensures that condition assignment is reproducible and documented. The selected order is saved in the participant log file.

No formal blinding is involved. Participants are not informed about the specific study hypotheses and will be debriefed after participation to minimize expectation-related effects.

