##### Planned sample size

3.4.2.1

Planned sample sizes are based on feasibility constraints typical for MEG studies in clinical populations and are intended to support initial mechanistic characterization rather than definitive effect size estimation. The overall clinical recruitment target is *N* = 30, with a planned minimum of *N* ≥ 15 in each diagnostic group (depressive disorders */* adult ADHD). Recruitment will continue until these targets are reached or until recruitment is no longer feasible within the project timeline.

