### Statistical analysis plan (overview)

3.9

Condition will be modeled as a within-subject factor with three levels: mindfulness/body scan, relaxation/safe place imagery, and control/podcast. The choice of statistical procedure will depend on the structure and distribution of the measures derived, for example multilevel models, parametric tests, or non-parametric tests. Repeated-measures ANOVA will be used for complete within-subject datasets when model assumptions are sufficiently met. Linear mixed-effects models will be used when appropriate to account for incomplete condition-level data, unequal numbers of usable observations, participant-level variability, or additional covariates such as condition order or medication status. If substantial deviations from model assumptions occur, for example due to pronounced non-normality, influential outliers, or distributional characteristics that are not adequately addressed by standard corrections or transformations, robust or non-parametric sensitivity analyses may be considered and explicitly reported.

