### Anticipated limitations and feasibility considerations

4.3

Several limitations are inherent to the proposed design. MEG recordings impose constraints on movement and overt speech, requiring rigorous artifact handling and limiting the interpretability of speech-related analyses, which are therefore treated as exploratory. Clinical populations are heterogeneous, and recruitment feasibility may constrain sample sizes, particularly for subgroup analyses. Consequently, population-level comparisons are intended to provide initial mechanistic characterization rather than definitive diagnostic differentiation. Furthermore, the single-session design focuses on acute regulatory processes and does not address longer-term intervention effects or clinical change over time.

In addition, the protocol includes a single standardized stress induction administered prior to the intervention phase, framed as a regulatory challenge to elicit a comparable initial perturbation across participants, to avoid repeated stress exposure in clinical populations and to maintain feasibility within a single-session MEG protocol. Because the stress induction occurs once and the three auditory conditions unfold afterwards in a randomized way, time-related effects such as recovery from the initial challenge, habituation, fatigue, or carryover across the session cannot be fully excluded. The block-randomized condition order is intended to reduce systematic bias by distributing such time-related effects across mindfulness, relaxation, and control conditions; however, residual carryover effects remain a consideration when interpreting condition-related differences within the acute experimental context.

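### Balance of condition over session position is not guaranteed at 15 per diagnostic group; complementary Latin-square blocks would secure it without extra participants

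*Protocol article*

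**What the plan says.** Section 3.3 describes the order mechanism in some detail. A random number generator produces one matrix per diagnostic group before data collection, and the script reads the row that matches the participant's sequential number in the group. The balance claimed is limited: "This procedure supports a balanced distribution of condition orders as far as possible within each diagnostic group". Sections 3.2 and 4.3 call the order block-randomized and section 3.3 calls it counterbalanced. No block size is given, and nothing is said about an incomplete last block.

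On size, section 3.4.2.1 states: "The overall clinical recruitment target is *N* = 30, with a planned minimum of *N* ≥ 15 in each diagnostic group". It adds: "Recruitment will continue until these targets are reached or until recruitment is no longer feasible within the project timeline".

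Section 4.3 concedes that recovery, habituation, fatigue and carryover may act across the session, and names order as the safeguard: "The block-randomized condition order is intended to reduce systematic bias by distributing such time-related effects across mindfulness, relaxation, and control conditions".

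In section 3.9, "Condition will be modeled as a within-subject factor with three levels". Repeated-measures ANOVA is used for complete data when its assumptions hold. Condition order appears only as an example of a covariate for mixed models, which are used where appropriate.

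**The concern.** There is one stress induction, before all three conditions, so a later position means more time to recover. If one condition sits later on average than another, part of the recovery is counted as a condition effect. The plan's stated protection is the distribution of orders, but the mechanism it describes does not guarantee an even distribution over positions at the planned group size. Adjustment in the model would be a second protection, and the plan leaves it optional. The separate ADHD and depression analyses are the most exposed, because 15 people carry each estimate.

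**Working it through.** **Inputs.** Three conditions (section 3.9); a minimum of 15 per group and a target of 30 (section 3.4.2.1); separate random matrices (section 3.3). The sample size rests on feasibility, so there is no power figure to reproduce; 15 + 15 = 30 agrees. Two assumptions are mine: all six orders are used, and the block size is six.

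**Divisibility.** Orders: 3! = 6. 15/6 = 2.5, so the six orders cannot be equally frequent within a group. 30/6 = 5, so they can be over both groups. Position balance needs only a multiple of three: 15/3 = 5, so each condition can stand five times in each position within a group.

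**One group of 15: two blocks of six plus three different orders at random.** There are C(6,3) = 20 possible remainders:
- 2 give exact balance (5/5/5 for every condition);
- 12 give a largest difference in mean position of 2/15 = 0.13;
- 6 give a largest difference of 4/15 = 0.27.

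In the 18 unbalanced cases the cells run from 4 to 6 instead of 5. Example of a worst case: body scan 6/5/4 over positions 1/2/3 has mean (6 + 10 + 12)/15 = 1.87. Podcast 4/5/6 has mean (4 + 10 + 18)/15 = 2.13.

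**Pooled 30, remainders drawn independently.** Of 20 × 20 = 400 pairs, 22 (5.5%) give full cell balance. The mean largest gap is 0.11. The maximum is 0.27, in 6 of 400.

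**Size of the bias without adjustment.** Bias = gap × drift per position. The documents give no drift, so a range is assumed, in residual SDs per position. At the worst gap of 4/15:
- drift 0.2: 0.05 SD;
- drift 0.5: 0.13 SD;
- drift 1.0: 0.27 SD.

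The standard error of a two-condition contrast at n = 15 is √(2/15) = 0.365 SD, so a drift of 0.5 gives 0.133/0.365 = 0.37 standard errors. For the mean pooled gap at the same drift: 0.106 × 0.5 = 0.053 SD, against √(2/30) = 0.258 SD, or 0.21 standard errors.

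**Cost of adjusting.** In a least-squares model with participant, condition and position, the variance of a condition contrast rises by a factor of at most 1.018 over the 20 remainders.

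**Check of the proposed construction.** Let A = [1 2 3], [2 3 1], [3 1 2] and B = [1 3 2], [2 1 3], [3 2 1]. Each puts every condition once in every position.
- ADHD 3×A + 2×B and depression 2×A + 3×B: every condition is 5/5/5 by position in each group.
- Pooled: every order occurs 3 + 2 = 5 times, and every ordered adjacent pair 6 + 4 = 10 times.
- Losing one participant, say with [1 2 3], leaves position totals of 29, 28 and 27 over 14 people, a gap of 2/14 = 0.14.

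**The case against.** A reader might infer that, because 15 is not a multiple of six, position is confounded with condition. That does not follow. Unequal order frequencies are compatible with exact position balance, and a single separately generated matrix can achieve it with two blocks of six plus one Latin square. Coordination between groups adds only equal order and adjacent-pair frequencies in the pooled sample. Even in the unbalanced cases, position remains estimable.

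A reader might also note that podcast is never first in the three example rows of section 3.3. Those rows are offered to explain the coding and say nothing about the actual matrix or its last rows.

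A third tempting step is to assume unrestricted random draws. The mean largest gap at n = 15 would then be 0.44, with a 95th percentile of 0.87: at a drift of 0.5, 0.87 × 0.5/0.365 = 1.2 standard errors. Descriptions of the order as block-randomized and counterbalanced argue against this.

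It is also fair to say that the sentence in section 3.3 is not false, that the unseen script may already use a Latin-square remainder, that order is named as a possible covariate, and that section 3.9.4 treats subgroup comparisons cautiously. For one fixed contrast, only 2 of the 20 remainders reach 0.27, the mean absolute gap is 0.11, and the expected signed gap is zero. All of this limits the size of the point. What remains is that the described mechanism does not secure the balance on which section 4.3 leans, and that adjustment is not promised.

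**Conclusion.** The point holds as a modest design improvement. Position balance at 15 per group is possible but not guaranteed. Under blocks of six with a random remainder it fails in 18 of 20 cases per group, by 0.13 or 0.27 of a position, and on average by 0.11 in the pooled 30. The resulting bias is at most about 0.37 standard errors per group at an assumed drift of 0.5 SD per position, and only if position is left out of the model. These figures rest on the assumed block size, on random and independent remainders, and on the assumed drift. They show a small avoidable bias; the documents do not support a claim of full confounding.

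**What to change.** Build each matrix from blocks of three that are Latin squares, using A and B as defined above: ADHD 3×A + 2×B and depression 2×A + 3×B, with rows shuffled within each block. Beyond 15 in a group, continue with alternating A and B blocks. State the block structure in section 3.3.

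In section 3.9, commit to position as a fixed effect in every condition model, including those for complete data. This is needed even with the better matrices, because early stopping (section 3.4.2.1) and outcome-specific exclusions (sections 3.7.7 and 3.9.2) will break exact balance.

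The cost is two regenerated matrices and no added participants. Within a group, adjacent pairs occur 6 versus 4 times, which offsets in the pooled sample. Position adjustment costs at most about 2% in variance under blocks of six and two residual degrees of freedom: with 15 complete participants, 45 − 15 − 2 = 28 becomes 26. Neither step removes carryover, which section 4.3 should continue to list as a limitation.

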### Participants and recruitment

3.4

#### Participants

3.4.1

Participants will be adults (≥ 18 years) from clinical populations, including individuals with depressive disorders or adult attention-deficit/hyperactivity disorder (ADHD). All participants must be fluent in German to ensure comprehension of instructions and questionnaires and must be able to provide informed consent.

#### Recruitment

3.4.2

Participants will be recruited via social media, email, and cooperation with clinical partners and outpatient services, subject to availability and ethical approval. Interested individuals will be able to register through an online link, where they will receive initial study information and be screened for basic exclusion criteria. Individuals who appear eligible will then be invited to an appointment with trained clinical personnel at the university outpatient clinic. This appointment will be used to verify the indicated diagnosis using structured clinical diagnostic interviews, ensuring that diagnostic assessment is conducted consistently across participants.

##### Planned sample size

3.4.2.1

Planned sample sizes are based on feasibility constraints typical for MEG studies in clinical populations and are intended to support initial mechanistic characterization rather than definitive effect size estimation. The overall clinical recruitment target is *N* = 30, with a planned minimum of *N* ≥ 15 in each diagnostic group (depressive disorders */* adult ADHD). Recruitment will continue until these targets are reached or until recruitment is no longer feasible within the project timeline.

#### Diagnostic assessment

3.4.3

Clinical diagnoses will be established using the German clinical version of the Structured Clinical Interview for DSM-5 Disorders, Clinician Version (SCID-5-CV; Beesdo-Baum et al., 2019), conducted by trained personnel.

Current medication use is recorded for all participants, including medication type/name and dosage. This information is collected during the initial online screening and reassessed on the study day as part of the pre-experiment questionnaire to ensure accuracy and completeness. Medication use is not treated as a general exclusion criterion to reflect the clinical reality of the target populations and to support ecological validity. However, participants with recent changes in medication within the last four weeks prior to participation are excluded to reduce variability related to unstable pharmacological effects. Medication status will be considered in the statistical analyses, for example by including it as a covariate in relevant models and by conducting sensitivity analyses to assess the robustness of findings with respect to potential medication effects.

#### Inclusion criteria

3.4.4

Age ≥ 18 yearsAbility to provide informed consentSufficient German language proficiencyDiagnosis of depressive disorder or ADHD confirmed via SCID-5-CV interview

#### Exclusion criteria

3.4.5

Neurological disordersContraindications for MEG recording (e.g., non-removable ferromagnetic material, implanted medical devices)Recent changes in medication within the last four weeks prior to participationSevere hearing impairment

#### Healthy reference cohort (program-level)

3.4.6

In addition to the clinical samples described here, the preregistered NeuroPsychth program includes a healthy reference cohort assessed with the identical paradigm to provide normative benchmarks and enable integrative comparisons across health and psychopathology at the program level. No results from the healthy cohort are reported in the present manuscript.

### Experimental procedure

3.5

Data are collected in a single laboratory session conducted in the MEG facility. After informed consent, participants complete baseline questionnaires assessing demographic, psychological, and lifestyle variables. A brief stress induction task is administered, followed by a resting-state baseline period.

The stress induction task design is informed by the Salzburg Mobile Stress Induction (SMSI), in which matrix reasoning tasks have been shown to elicit stress responses, including increases in negative affect (Vikoler et al., 2025). Prior findings indicate that stress-related changes already emerge after the first task block, supporting the use of a brief, single-block implementation in the present study. Stress is induced in the current study using matrix reasoning items. The matrix reasoning items period lasts 144 s and consists of one block with 12 items, each presented for 12 s under time pressure. In each trial, participants are required to complete an incomplete visual pattern by selecting the correct option from multiple alternatives, consistent with standard matrix reasoning paradigms. Immediate performance feedback is provided after each trial in the form of salient visual feedback indicating correct or incorrect responses, thereby increasing evaluative pressure and task engagement. The total stress induction task lasts up to approximately 5 min, including instructions, an example item, feedback, and transitions. This duration is given as an approximate upper limit because some elements are participant-paced, including reading the instructions, completing the example item, and advancing through feedback screens. In addition, the task is introduced as an intelligence-related performance task during the study briefing to further enhance its evaluative character. Full debriefing is provided at the end of the experiment.

The stress induction task is intentionally designed to be brief and moderate intensity. This reflects the aim of the study to investigate regulation processes following a controlled perturbation rather than prolonged stress exposure. A mild stressor is intended to induce a transient increase in arousal while minimizing fatigue and participant burden, which is particularly important when working with clinical populations. Furthermore, the stress induction task serves a methodological purpose by reducing interindividual variability in baseline arousal. By bringing participants to a more comparable initial physiological and affective state prior to the intervention phase, it facilitates the interpretation of condition-related changes across neural, autonomic, and subjective measures.

Because the stress induction task is administered prior to MEG recording, task-related movement or response behavior during the task does not directly contaminate the subsequent MEG recordings. To ensure participant safety and tolerability, participants are explicitly asked after the stress induction whether they feel able to continue the study.

In addition, subjective stress and relaxation levels are assessed at predefined time points to monitor the effectiveness and acceptability of the manipulation.

Participants then complete three auditory conditions—mindfulness (body scan), relaxation (safe place imagery), and a control condition (podcast)—presented in randomized order. Each condition lasts approximately 10 min. During the entire session, magnetoencephalography (MEG), cardiac activity (electrocardiography, ECG), and respiration (respiratory belt) are recorded continuously.

After each auditory condition, participants provide brief verbal responses to standardized reflection questions and complete momentary ratings of stress and relaxation at predefined time points. At the end of the session, participants complete additional questionnaires and are debriefed.

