### Study contribution and rationale

4.1

This study protocol specifies a standardized, within-subject experimental framework to examine acute regulation after stress induction during brief mindfulness- and relaxation-based interventions in clinical populations. By combining magnetoencephalography with cardiac activity, respiration, and repeated subjective ratings within a single session, the protocol is designed to characterize condition-related regulation across neural, autonomic, and experiential levels under tightly controlled conditions. The focus is on short, commonly used interventions delivered in a standardized auditory format, allowing differentiation between mindfulness, relaxation, and control conditions within the same individuals.

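### The pooled condition contrasts measure acute effects of the recordings in a session that began with a stressor; they do not by themselves show regulation of induced stress, as Sections 3.5 and 4.1 suggest

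*Protocol article*

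**What the plan says.** Section 3.5 sets the sequence: "A brief stress induction task is administered, followed by a resting-state baseline period". On the task itself: "The matrix reasoning items period lasts 144 s and consists of one block with 12 items, each presented for 12 s under time pressure", and "The total stress induction task lasts up to approximately 5 min, including instructions, an example item, feedback, and transitions". The intended effect is modest and short: "A mild stressor is intended to induce a transient increase in arousal while minimizing fatigue and participant burden". Three auditory conditions follow in randomized order, and "Each condition lasts approximately 10 min". Between them come only a short spoken reflection and ratings.

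The same section says the stressor serves the study of regulation following a controlled perturbation. It adds a methodological purpose: "By bringing participants to a more comparable initial physiological and affective state prior to the intervention phase", the task should make condition-related changes easier to interpret. Section 4.1 describes the framework as one "to examine acute regulation after stress induction during brief mindfulness- and relaxation-based interventions in clinical populations".

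Section 4.3 acknowledges that "the protocol includes a single standardized stress induction administered prior to the intervention phase". It explains this by burden and feasibility, names recovery, habituation, fatigue and carryover as possible, and relies on randomized order to spread them over conditions. Section 3.9 models condition as a three-level within-subject factor, uses repeated-measures ANOVA for complete data when assumptions hold, and mentions condition order only as an example covariate for mixed models used when appropriate.

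**The concern.** A claim about regulating induced stress needs induced stress to be present when the recording starts. Here a rest period of unstated length separates the stressor from the first block, and the second and third blocks start from whatever state the previous recording and reflection left. The planned contrast averages over all three positions.

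If the stress response has largely gone by block onset, a null contrast says little about stress regulation, because there was little left to regulate. A positive contrast could equally be an effect of the recording on a resting person. Neither result would separate these readings without evidence on the stress level at block onset and on whether the condition effect changes with position.

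**Working it through.** **Inputs from the protocol article.** One stressor; 12 items of 12 s; whole task up to about 5 min; rest period of unstated length; three blocks of about 10 min; reflection and ratings of unstated length between blocks (all Section 3.5); orders counterbalanced as far as possible within each diagnosis (3.3); N = 30, at least 15 per diagnosis (3.4.2.1); two-tailed alpha 0.05 (3.9.3).

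**The plan's own figure.** 12 × 12 s = 144 s, as stated.

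**Position.** This needs no assumption about decay. Of three blocks per person, one follows stress and rest with no other recording in between. With the six orders used equally, 30/6 = 5 people per order, and two orders start with each condition, so 2 × 5 = 10 people per condition have it first. Within a group of exactly 15 the six orders cannot be used equally (15/6 = 2.5); cycling through them gives first-position counts of 6, 5 and 4.

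**What the pooled contrast estimates.** Let δ1, δ2, δ3 be the difference between two conditions at positions 1, 2 and 3, with any carryover included in δ2 and δ3. Under balanced orders a purely additive position effect cancels, and the pooled contrast estimates (δ1 + δ2 + δ3)/3. If the effect is the same at each position, nothing is lost. If, as an extreme case, a difference existed only in the first block, the pooled contrast would show δ1/3. A condition-only ANOVA cannot tell these cases apart.

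**Timing.** Onset of block k after the stressor = rest + (k − 1) × (10 min + gap). Assuming rest of 2 to 10 min and gaps of 0 to 3 min, blocks start at about 2–10, 12–23 and 22–36 min.

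**Residual stress.** Assume exponential decay with half-life h and no effect of the previous recording. Relative to block 1, blocks 2 and 3 start with 2^(−10/h) and 2^(−20/h) when the gap is zero. The mean over positions is (1 + 2^(−10/h) + 2^(−20/h))/3.

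| Half-life (assumed) | Block 2 | Block 3 | Mean over blocks |
|---|---|---|---|
| 5 min | 25% | 6% | 44% |
| 10 min | 50% | 25% | 58% |
| 20 min | 71% | 50% | 74% |
| 60 min | 89% | 79% | 89% |

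With 3-min gaps, block 2 falls to 16%, 41%, 64% and 86%, and block 3 to 3%, 16%, 41% and 74%. The rest period also matters for block 1 itself: with 10 min of rest and h = 5 min it starts with 2^(−2) = 25% of the initial rise; with 2 min and h = 60 min, 2^(−2/60) = 98%.

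**Could first-position data carry the claim?** That contrast is between people, about 10 per condition. The detectable standardized difference at 80% power is (1.96 + 0.84) × √(2/10) = 1.25, and power at d = 0.5 is about 20%. The pooled within-person contrast detects dz = (1.96 + 0.84)/√30 = 0.51. The two scales coincide only at a within-person correlation of 0.5, but the first-position contrast is clearly too weak to stand alone.

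**Evidence on the stress level.** Ratings are scheduled on arrival, after stress, after baseline, after each condition and at the end (3.7.5). Section 3.5 places the stressor before MEG recording, yet also says MEG, ECG and respiration run through the whole session. These statements need reconciling. If ECG and respiration start only with MEG, the ratings are the main evidence that stress rose.

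**The case against.** The strongest reply is that the protocol does not promise what a critical reader may hold it to. One might infer that every block is supposed to start stressed and that at most one of three does. The documents support neither half. The comparability sentence refers to the state before the intervention phase as a whole, and all three blocks do follow the stressor, two of them less directly. Whether later blocks keep little or most of the response depends on a decay time and a rest length that the article does not give; at a 60-minute half-life most of it would remain.

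It is also fair to say that the primary aims, question and hypotheses (2.1 to 2.3) concern differences between conditions, not stress recovery; that Section 4.3 discloses the single stressor, recovery and carryover, with reasons; that Section 4.4 restricts inference to acute regulation in this paradigm; and that the ratings are already meant to monitor the manipulation. A formal decision rule could sit in the preregistration, so its absence here is not an error.

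All of that stands and limits the point. What it does not answer is that randomized order deals with bias between conditions, not with whether stress is present to be regulated, and that Sections 3.5 and 4.1 are not qualified by 4.3.

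**Conclusion.** The point holds as one about interpretation and wording. By design, one block in three per person, about 10 of 30 people per condition under balanced orders, follows stress and rest without another recording in between. The pooled contrast is therefore an acute effect of the recordings, averaged over positions, in a session that began with a stressor. Calling it regulation of induced stress needs further evidence, and the condition-only ANOVA provides none.

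The loss of stress at block onset cannot be fixed from the documents: the range of 44% to 89% of the post-rest level rests on assumed half-lives, zero gaps and no effect of the previous recording. A reader might also infer that the condition comparisons are biased or invalid. They are not, provided orders are balanced and recovery is additive.

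**What to change.** 1. In Section 3.9, report the arrival, post-stress and post-baseline stress ratings as a manipulation check, with confidence intervals for the change from arrival to post-stress and from arrival to post-baseline. Interpret results as stress regulation only if stress rose after the task and was still raised after baseline. Note that arrival ratings may themselves be raised by anticipation.
2. Include block position in the condition models for complete as well as incomplete data, and report condition-by-position estimates with confidence intervals, labelled exploratory. Do not rest the stress claim on first-position contrasts alone.
3. Reword Sections 3.5 and 4.1 to match the scope in 4.4 and the caveat in 4.3.

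The procedure, the sample and the data collected stay as they are. The cost is a narrower headline claim and a few degrees of freedom: 2 for position and (3 − 1) × (3 − 1) = 4 for the interaction. The interaction estimates will be imprecise at N = 30 and cannot be cleanly separated from carryover, so they inform the interpretation and do not test it.
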